### Data collection

Clinical, imaging, and follow-up data will be collected prospectively in the case report forms (Additional file 4) and reserved in the O-trial online database (https://plus.o-trial.com/), which is daily maintained by [name] and [name]. The O-trial online database is a secure, password-protected database and can be only accessible to authorized project staff.

Details of the evaluation items and time points have been shown in Table 2. During CAPOX, blood routine and biochemistry will be examined weekly to detect potential hematopoietic inhibition or liver or kidney function impairment. Tumor markers, at least including CEA and CA19-9, will be recorded every cycle. Imagological examination, including chest CT, abdominal enhanced CT, rectal MRI, and TRUS will be re-evaluated every 2 cycles.

**Table 2 Tab2:** Details of the evaluation items and time points

	Screening	After 2 cycles of CAPOX (4 cycles)	Preoperative evaluation	Intraoperative evaluation	Postoperative evaluation	Follow-up visit
Colonoscopy	×					
Chest CT	×	×	×			×
Abdominopelvic enhanced CT	×	×	×			×
Pelvic MRI	×	×	×			
TRUS	×	×	×			
Blood routine	×	×	×			×
Blood biochemical indicators	×	×	×			×
Tumor markers^a^	×	×	×			×
Intraoperative complications				×		
Blood loss				×		
Operation time				×		
Surgical approach				×		
Perioperative complications					×	
Patient recovery					×	
Hospitalization time					×	
pTRG					×	

*TRUS* Transrectal ultrasonography, *pTRG* Pathological tumor regression grade

^a^At least includes CEA and CA19-9

Surgical information including tumor location and involvement, intraoperative stages, lymph node metastasis, operation times, intraoperative time, and complications will be recorded in detail in the surgical records. Perioperative complications are stratified by the Clavien-Dindo system. Resected rectal specimens will be fixed on a foam plate and sent to pathologists to determine the circumferential resection margin (CRM) and pTRG).

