Adverse events mainly include tumor progression and serious chemotherapy adverse effects during CAPOX. Tumor progression is defined as a tumor longitudinal size increase greater than 20%. Patients will be advised to withdraw from the trial if the tumor is determined a progressive disease (PD). The chemotherapy-related adverse effect is graded according to CTCAE 5.0, and adverse effects graded 3–4 are defined as serious adverse effects. The occurrence and recording of adverse reactions are responsible for the sub-center and follow the principles below:If a 1/2° adverse reaction occurs, no special treatment is required.Capecitabine/oxaliplatin should be discontinued and corresponding symptomatic treatment should be given when 4° leukopenia, 3° adverse reactions of the digestive tract, 2° anemia and thrombocytopenia, and 2° liver and kidney function impairment occur. If the adverse reactions decreased to 0 ~ 1° within 5 days after treatment, the original dose of capecitabine/oxaliplatin can be restored. Otherwise, capecitabine/oxaliplatin should be reduced to 75%. Capecitabine/oxaliplatin treatment should be discontinued if these adverse reactions persist for more than 3 days after symptomatic treatment and dosage reduction or other adverse reactions above 2° occur.When other 3° adverse reactions occur, the treatment principle is the same as the corresponding 2° adverse reactions.Chemotherapy should be stopped in case of any 4° adverse reactions other than leukopenia occurring.

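### The 75% dose branch has no recovery condition, so as worded chemotherapy can restart at a reduced dose while the reaction that caused the hold is unresolved

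*Protocol article*

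**What the plan says.** The rule stands in the Protocol article, Monitoring and reporting, and works in four steps.

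1. **Hold.** Capecitabine/oxaliplatin "should be discontinued and corresponding symptomatic treatment should be given when 4° leukopenia, 3° adverse reactions of the digestive tract", and also when "2° anemia and thrombocytopenia, and 2° liver and kidney function impairment occur".
2. **Full dose.** If the reaction has fallen to grade 0–1 "within 5 days after treatment, the original dose of capecitabine/oxaliplatin can be restored".
3. **Reduced dose.** "Otherwise, capecitabine/oxaliplatin should be reduced to 75" percent.
4. **Persistence stop.** Capecitabine/oxaliplatin "treatment should be discontinued if these adverse reactions persist for more than 3 days after symptomatic treatment and dosage reduction".

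Two further statements in the section matter. On severity, "adverse effects graded 3–4 are defined as serious adverse effects". On the highest grade, "Chemotherapy should be stopped in case of any 4° adverse reactions other than leukopenia occurring".

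On monitoring, Data collection states that during CAPOX "blood routine and biochemistry will be examined weekly to detect potential hematopoietic inhibition or liver or kidney function impairment". Under Randomization and intervention, oxaliplatin 130 mg/m² is given on day 1 and capecitabine 1000 mg/m² twice daily on days 1 to 14 of a 21-day cycle.

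**The concern.** The recovery condition belongs only to the full-dose branch. The 75% branch is whatever is left over, and that includes patients who have not recovered at all. Applied literally, the rule lets a center give chemotherapy to a patient who still meets the criterion for withholding it.

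The stake is patient safety. Monitoring and reporting leaves safety monitoring to each sub-center, and the trial is planned for fourteen hospitals, so the sentence will be read by many teams and may be read differently. The case that matters most is a patient still at grade 4 leukopenia or grade 3 digestive toxicity.

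**Working it through.** The plan gives no figure to reproduce. The check reads the rule as a decision tree and then follows it through a cycle.

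**Step 1: who reaches the 75% branch.** At the 5-day decision, any grade above 1 goes to that branch.

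- Grade 2 triggers (anemia, thrombocytopenia, liver, kidney): not recovered means grade 2 or higher, so the patient is still at or above the hold grade.
- Leukopenia (trigger grade 4): not recovered means grade 2, 3 or 4. The branch mixes improved patients with patients still at the trigger. The stop for grade 4 reactions does not catch the latter, because it excepts leukopenia.
- Digestive reactions (trigger grade 3): not recovered means grade 2 or 3, again a mixture. A rise to grade 4 would stop chemotherapy.

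**Step 2: does another sentence supply the missing condition?** None does. The persistence stop points the other way: a reaction can persist after a dose reduction only if the reduction may begin while it is present.

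**Step 3: timing within a cycle.** The article says only that blood tests are weekly and gives no restart day. Assumptions: tests on days 8 and 15, or alternatively 7 and 14; the hold starts on test day d; the 5 days run from d; and reduced dosing could start on d+6. The persistence limit of more than 3 days is then passed after d+8. The next scheduled test is on d+7, which is 7 − 5 = 2 days after the decision. The next cycle's day 1 is day 1 + 21 = 22.

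Reduced doses: 0.75 × 1000 = 750 mg/m² capecitabine; 0.75 × 130 = 97.5 mg/m² oxaliplatin.

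| Hold from day d | Decision d+5 | Reduced dosing possible d+6 to d+8 | What falls due in that window | Next scheduled test d+7 |
|---|---|---|---|---|
| 7 | 12 | 13–15 | capecitabine days 13–14: 2 × 2 = 4 doses of 750 mg/m² | 14 |
| 8 | 13 | 14–16 | capecitabine day 14: 1 × 2 = 2 doses of 750 mg/m² | 15 |
| 14 | 19 | 20–22 | day 22: oxaliplatin 97.5 mg/m², capecitabine 750 mg/m² twice daily | 21 |
| 15 | 20 | 21–23 | day 22: oxaliplatin 97.5 mg/m²; capecitabine 750 mg/m² twice daily from day 22 | 22 |

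**Step 4: what the table shows.** For mid-cycle holds the possible exposure is 2 to 4 reduced capecitabine doses. Some or all of these come before the next scheduled blood result. For late-cycle holds oxaliplatin falls due inside the window, but a scheduled result arrives on the infusion day or the day before. Blood tests do not inform the digestive trigger, which needs clinical assessment.

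**The case against.** The strongest reply is that the prose is terse and does not order a restart. The drugs have already been stopped, 75% names a dose and not a day, and nothing says the hold ends on day 5. The sentence may simply mean recovery later than day 5. That reading is possible, and it is why a reader who infers that the plan instructs centers to re-dose unrecovered patients goes too far. But the text does not state the milder meaning, and the persistence sentence fits it poorly. The ambiguity itself needs removing.

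It can also be said that an article leaves restart timing to the full protocol. That is fair for detail which is merely absent. Here the article states the rule with grades, days and a percentage, and the stated branch is incomplete.

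Three points in defence stand and limit the concern.

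- **Oxaliplatin.** A reader might infer that an infusion would be given with no laboratory check. Under the assumed test days a scheduled result falls on day 21 or 22, and an unrecovered result would again meet the hold criterion.
- **Grade 2 triggers.** Four of the six triggers are at grade 2, and a reader might take that count as the size of the danger. It counts list items, not patients. The section opens by saying that grade 1 and 2 reactions generally need no special treatment, so reduced dosing through a grade 2 reaction may be deliberate. The documents do not show it to be unsafe.
- **Other safeguards.** There is the 3-day persistence stop, the stop for grade 4 reactions other than leukopenia, and withdrawal on medical grounds when risks exceed those expected. These limit exposure. The persistence stop acts only once the dose has been reduced, so it does not prevent a first reduced dose.

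**Conclusion.** The point holds and is worth correcting. The 75% branch lacks a recovery condition, and the next sentence implies that reduced dosing may start before the reaction has resolved. The firm safety concern is confined to grade 4 leukopenia and grade 3 digestive reactions. For the grade 2 triggers the finding is a milder inconsistency between the branch and its own hold criterion.

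The documents do not allow an estimate of how many patients would be affected. Under the assumed schedules the mid-cycle exposure is 2 to 4 capecitabine doses of 750 mg/m², with oxaliplatin at issue only when a day 1 falls due, at about the time of a scheduled blood result. These figures depend on the assumed test days and on a restart the day after the 5-day decision, neither of which the article fixes. The primary endpoint, the non-inferiority margin and the sample size are unaffected.

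A reader might also infer that the 3-day stop is faulty and must be replaced. The defect does not require that.

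**What to change.** Change the sentence to read: *Otherwise, treatment stays on hold until the reaction recovers to 0–1° (confirmed by a repeat blood test for laboratory triggers) and then resumes at 75%.*

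Keep the 3-day persistence stop, applied to reactions that recur on the reduced dose. Because an open-ended hold would leave patients who never recover without a stopping rule, the investigators should also set a maximum hold after which treatment is discontinued. The documents give no basis for choosing its length.

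The cost is some longer holds, an occasional repeat blood test and notice to the centers. As a change to a dosing rule it would count as a substantive amendment, which under Protocol amendments goes to the review board and onto the registry. In setting the maximum hold, the investigators should note that Data-analysis moves four-cycle patients who received fewer than 3 cycles because of adverse effects into the two-cycle analysis, so a limit that changes how many cycles are delivered could shift some patients between the groups. Trial status gives December 2023 as the expected end of recruitment, so the benefit depends on how many patients have yet to complete chemotherapy.

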### Patient and public involvement

Patients or the public are excluded from the design of the trial and the selection of endpoint parameters since the determination of tumor stage and decision of whether NCT should be implemented is a crucial step that needs professional backgrounds. Patients are excluded from the recruitment and conduct of the trial either. The schedule of the current study has been listed in Additional file 5. The results of the present study will be published via medical journal(s). Participants of the study will be informed of the outcomes by local monitors via phone or letter.

### Protocol amendments

Substantive amendments to the current version of the protocol will be detailed and submitted to the institutional review board committee at the West China Hospital, Sichuan University, for approval. We will also update the amendments on ClinicalTrials.gov.

## Discussion

NCRT has been used widely to improve both local control and outcomes in patients with rectal cancer, but it also brought side effects related to the therapy.

Given our previous phase II clinical study found that NCT alone achieved good tumor response rates in patients with low- and intermediate-risk stage II/III rectal cancer, and predicting tumor response to NCT was feasible at an early treatment phase, we conducted this prospective, non-inferior, randomized, controlled study (COPEC trial) to verify the tumor pathological response rate in patients with 2 cycles of CAPOX was not inferior to that of 4 cycles and the determination of chemotherapy-insensitive population at early cycles is feasible.

For rectal cancer (RC), stratified treatment has been increasingly recommended and included in ESMO guidelines [19]. However, the criteria of stratification still need to be further explored, and the curative effect of each stratification has still not been determined. For high-risk rectal cancer, NCRT has been proven with reduced local recurrence rate, although improved overall survival has not been proven. For intermediate-low-risk rectal cancers, our previous study has found that patients diagnosed with stage II/III rectal cancers without high-risk factors were less likely to benefit from radiotherapy. At the same time, radiotherapy did not bring significant 5-year survival benefits. Therefore, a consensus has been reached that patients with low- and intermediate-risk stage II/III rectal cancer could consider dispensing with preoperative radiotherapy, and chemotherapy alone might achieve an accepted local control.

For distant control of tumor cells, FOWARC, GRECCAR 4, and other trials [26–29] explored whether radiotherapy-free neoadjuvant chemotherapy alone could improve patients prognosis and have observed the pathologic complete response (pCR) ranging from 7 to 12.2%. These studies included patients with stage II/III rectal cancer in different strata, without specific stratification for risk factors. In the exploration of combined targeted therapy, studies showed that in patients with advanced stages who have risk factors such as ≥ T3c, N2, MRF ( +), etc., even if targeted drugs were used in combination, the pCR rate was still lower by 13% [30] and 4% [31]. However, if only patients with low- and intermediate-risk factors were included in targeted therapy, the pCR rate could reach 25% [32] and 20% [33]. A study of the National Cancer Center of Japan found that the local recurrence rate of high-risk rectal cancer patients with NCT alone was as high as 19.6%, and the local recurrence rate of those with poor response to chemotherapy was as high as 34% with a low survival rate [34]. The PROSPECT study included relatively low-risk (non-T4, N2) stage II/III rectal cancer patients [34] and obtained a pCR rate of 25%, despite some high-risk T3c-d in T3 population [35] being included. Therefore, current studies suggest that preoperative NCT alone may benefit patients with low- and intermediate-risk stage II/III rectal cancer, but there is still a lack of more detailed stratification and evidence for pathological criteria. For this reason, we have conducted a phase II study which included low- and intermediate-risk stage II/III rectal cancer for NCT alone and found that the proportion of patients with tumor shrinkage and downgrade after only 4 cycles of NCT for low- and intermediate-risk stage II/III rectal cancer was 78.7%, with the pCR rate of 21.3% [16].

At present, there are retrospective and small prospective studies [27, 28, 32, 34, 36] that have shown that chemotherapy alone could still achieve an excellent prognosis for low- and intermediate-risk stage II/III rectal cancer, and there are also large RCTs that are validating whether neoadjuvant chemotherapy alone non-inferior to neoadjuvant chemoradiotherapy for low-risk stage II/III rectal cancer [37]. Although the results have not yet been announced, it is speculated from the existing evidence that NCT alone can achieve relatively good results for patients with low- and intermediate-risk. However, the evaluation time of chemotherapy effects in previous studies was 12 weeks after chemotherapy (6 cycles of FOLFOX or 4 cycles of CAPOX), which was relatively long. Patients who are not sensitive to chemotherapy may need to convert to surgery, radiotherapy, and other intensive treatments in advance, and the relatively long-term chemotherapy may lead to delay of patients’ opportunity to receive necessary treatment, causing a series of oncology consequences and acquiring unnecessary adverse effects of chemotherapy.

The power of the COPEC trial lies in its 2 verse 4 cycles’ design to acquire early pathological outcomes after NCT. Based on our previous phase II study, we hypothesize COPEC trial could obtain a good pathological response judgment in patients with low- and intermediate-risk stage II/III rectal cancer after 2 cycles of preoperative CAPOX chemotherapy. The major challenge of the COPEC trial is the difficulty in patient enrollment, which is mainly due to the worry that 2-cycle CAPOX maybe not be powerful enough in dealing with local advanced rectal cancer. However, we have proved in the previous phase II study that obvious tumor morphological changes were observed after 2 cycles of preoperative CAPOX chemotherapy and those who responded poorly after 2 cycles of NCT would not benefit from 2 more cycles. So perhaps, in the future, the follow-up standard treatment plan for patients with low- and intermediate-risk rectal cancer may become NCT alone without radiotherapy combined with early assessment of tumor response and screening out those with poor response to NCT for further advanced treatment. We hope the COPEC trial could help in establishing a consensus standard of low- and intermediate-risk rectal cancer and the early identification of stage II/III rectal patients with low- and intermediate-risk who are poorly responding to NCT.

## Trial status

This paper reflects protocol version 1.2. dated 6 December 2021. The trial was first registered on ClinicalTrials.gov on 4 June 2021, with the last update posted on 16 March 2022 (NCT04922853). Participant recruitment began on 6 June 2021 and is expected to be completed in December 2023. Raw data are expected to be available for publication after the study via an open-access database.

## Data Availability

The study co-primary investigators ([name] and [name]) will provide the full study protocol, study data, and statistical code upon reasonable request and approval of an appropriate data-sharing agreement.

## Abbreviations

RC: Rectal cancer
RCTs: Randomized controlled trials
NCRT: Neoadjuvant chemoradiotherapy
NCT: Neoadjuvant chemotherapy
TME: Total mesorectal excision
AI: Artificial intelligence
NCCN: National Comprehensive Cancer Network
ESMO: European Society for Medical Oncology
MRF: Mesorectal fascia
pCR: Pathologic complete response
MRI: Magnetic resonance imaging
CT: Computed tomography
TRUS: Transrectal ultrasonography
CEA: Carcinoembryonic antigen
CA19-9: Carbohydrate antigen 19–9
TRG: Tumor regression grade
mrTRG: MRI tumor regression grade
pTRG: Pathological tumor regression grade
DWI: Diffusion-weighted imaging
ADC: Apparent diffusion coefficient
DFS: Disease-free survival
OS: Overall survival
MRD: Molecular residual disease
Life quality (EORTC-QLQ-C30): This sub-questionnaire contains the 2 items of the global quality of life dimension of the EORTC-QLQ-C30 questionnaire
Life quality (EORTC-QLQ-CR29): This questionnaire is developed to assess the quality of life in colorectal patients
I-PSS: International Prostatic Symptom Score
QOL: Quality of life
CTCAE: Common Terminology Criteria for Adverse Events
CRM: Circumferential resection margin
LR: Local recurrence rate
PD: Progressive disease
DR: Distant recurrence rate
ICF: Informed consent form
